## Abstract

**Background:**

Treatment delay in first episode psychosis is common. As general practitioners are the first point of contact for many individuals with first episode psychosis, they are well placed to detect the early symptoms and make urgent referrals to specialist secondary care services. However, early psychosis is often difficult to detect. The primary objective of the Redirect trial is to estimate whether an educational intervention targeted at general practitioners increases the general practitioner referral rate of young people with first episode psychosis to Early Intervention Services.

**Methods/design:**

This paper describes the design of a stratified-cluster randomised controlled trial of an educational intervention on first episode psychosis in primary care. The primary outcome is the number of general practitioner referrals of young people with first episode psychosis to Early Intervention Services. Secondary outcomes are duration of untreated psychosis, time to recovery, use of the Mental Health Act, and general practitioner consultation rate. Young people with first episode psychosis referred to Early Intervention Services will be recruited over a two-year period from 1 March 2004. Seventy-eight out of 89 eligible general practices were recruited. The educational intervention has been implemented and evaluated by general practitioners. The education was well received and considered relevant to clinical practice by the general practitioners.

**Discussion:**

The results suggest that the recruitment strategy and implementation of the educational intervention are feasible and acceptable in a primary care setting. The Redirect trial will provide robust information about the efficacy of an evidence-based complex educational intervention targeted at general practitioners on referral rates of young people with first episode psychosis to Early Intervention Services.

## Background

Studies have shown that young people with first episode psychosis (FEP) experience lengthy delays between the onset of psychotic symptoms and receipt of treatment [1,2]. The average period from first onset of psychosis to initiation of adequate treatment (duration of untreated psychosis, or DUP) is one to two years [3]. During this untreated period, irreversible biological, social and psychological damage may take place [2], and a delay in treatment is associated with poorer short-term outcome and slower recovery [1]. Early intervention in this 'critical period' [4] is therefore important for both patients and families. Strategies to reduce DUP include providing early access to specialist mental health services, such as early intervention services (EIS), and improving recognition of FEP by educating primary care professionals [5].

The integration of mental health and primary care services around the world, in developed as well as developing countries, has been widely advocated [6-10]. As part of this process, a range of national and international policy developments have occurred, with the aim of improving the identification and management of mental illness in primary care [11-18]. In the United Kingdom (UK), for example, standards two and three of the Mental Health National Service Framework [16] require primary care to provide effective identification, assessment, and treatment of people with mental illness, including appropriate early referral to specialist services. National guidance on schizophrenia [19] and the inclusion of mental health indicators for care of people with serious mental illness in the new GP contract [20] further strengthen the role and responsibilities of primary care by encouraging a more systematic approach to care, including the use of protocols and referral guidelines.

As part of the UK policy response to improve the early detection and treatment of FEP, in 2000, the NHS Plan prioritised the development of 50 "early intervention" teams across England and Wales to provide specialist mental health services for all young people aged 14–35 with a FEP [21]. General practitioners (GPs) are well placed to play a greater role in the identification and management of FEP, as they are usually the first point of patient contact [22], and GP involvement in the management of psychosis is associated with reduced use of the Mental Health Act[23]. However, primary care health professionals cannot refer to EIS without knowledge of FEP and an understanding of the EIS referral system.

The limited evidence base in this area has, however, consistently shown a need for improvement in the detection and management of FEP in primary care. Early detection is a challenge for many GPs, since psychosis does not present in "neat packages" and can take several months to emerge [24]. The prodrome largely consists of non-specific psychological and social disturbances of varying intensity, which is possibly why GPs experience difficulty in distinguishing FEP from normal adolescent behaviour [25,26]. GPs also experience uncertainty about how to identify FEP, treat FEP appropriately, and access specialist mental health services [25,26]. These data suggest the importance of training GPs to improve early detection and management of FEP to reduce the delay between onset of symptoms and initiation of treatment.

Recent reports indicate that promoting early detection in a community based setting can be successful [27,28]. A Scandinavian community education programme in the identification of FEP, for example, led to reduction in DUP from 1.5 years (mean) to 0.5 years [27,29]. However, the Redirect trial is the first randomised controlled trial aimed at educating GPs about FEP.

The Redirect study team designed an evidence based "complex" educational intervention that addressed the knowledge, skills, and attitudes of GPs about FEP. A refresher educational intervention was planned and implemented to reinforce knowledge and skills acquired in the initial educational intervention and to promote positive attitudes towards young people with FEP, given that most GPs see only one or two new people with FEP each year. The intervention is being used in a stratified-cluster randomised controlled trial to evaluate the effect of the educational intervention on GP referral rates of young people with FEP to EIS.

### Study aims

The primary aim of the Redirect trial is to estimate whether an educational intervention targeted at GPs increases the GP referral rate of young people with FEP to EIS.

## Methods/design

### Setting, eligibility and recruitment of practices

Ethics Committee approval was obtained from Sandwell & West Birmingham, South Birmingham and East Birmingham Research Ethics Committees. The Redirect trial was conducted in three Primary Care Trusts (PCTs) within Birmingham in the UK, which encompass the areas of Aston, Handsworth, Ladywood, Nechells, Sandwell, Small Heath, Sparkbrook, Sparkhill, Soho, and Washwood Heath. Eighty-nine general practices within these three PCTs with the authority to refer to EIS were eligible for inclusion to the trial. These included 74 general practices located within the catchment area of the Heart of Birmingham Teaching PCT (HoB tPCT), 14 practices within the catchment area of Eastern Birmingham PCT, and one practice within the catchment area of South Birmingham PCT.

Practice recruitment was facilitated by a letter to each practice from the study team and from the Chief Executive of the HoB tPCT, presentations by the second author at the HoB tPCT protected "learning time" sessions (where the PCT enabled GPs to close their practices and attend by paying for locum doctor cover) and an evening meeting attended by the practices within the catchment area of Eastern Birmingham PCT. Practices received a quarterly newsletter post randomisation during the study period. The newsletter was designed to encourage continued interest and participation in the Redirect trial.

Consecutive patients with FEP who are referred by the Redirect trial GPs to the two Birmingham EIS over a two-year period from 1 March 2004 to March 2006 are eligible for inclusion in the study. Patients must also be aged between 14 to 30 years, in line with the Mental Health Policy implementation guide for Early Intervention [30], and have an ICD-10 [31] chart diagnosis of schizophrenia or related disorders (F20, F22, F23, F25, F28, F31). The exclusion criteria are patients with a primary diagnosis of substance use disorder, mood disorder, or organic mental disorder, current criminal proceedings, serious concurrent physical illness, institutional residence, learning disability, or inability to provide informed consent (see Table 1).

**Table 1 T1:** Patient inclusion and exclusion criteria

*Inclusion criteria*

• First episode psychosis
• Aged 14–30 years
• (ICD-10: F20, 22, 23, 25, 28, 31)
• Living within the catchment area

*Exclusion criteria*

Patients with a history of prior psychosis in receipt of antipsychotic medication

Patients with a primary diagnosis of substance use disorder or organic disorder

Institutional residence

Patients with learning disability

Inability to provide informed consent

Patients with current criminal proceedings

Patients with serious concurrent physical illness

### Design and randomisation of general practices

The study is a stratified-cluster randomised controlled trial design [32,33]. The cluster design at practice level reduces the risk that the educational intervention delivered to GPs will be contaminated by interaction between GPs within a single practice. Practices were randomly allocated after stratifying by list size (more or less than 3,500 patients) and PCT (HoB or not). These strata were used to ensure balance on the number of practices where no referrals of FEP might occur and to account for the differential prevalence of FEP across the study area. Practices were randomly allocated to either the intervention (39 practices) or control group (39 practices) by NF, who was blind to practice identity, using computer generated random numbers. Figure 1 shows the trial profile summarising practice recruitment and retention.

**Figure 1 F1:**
[figure not shown]
GP enrolment, randomisation and flow of practices through trial

### The educational intervention

General practices were randomised to receive either the educational intervention on detecting FEP (intervention practices) or to an alternative educational session on cognitive behaviour therapy for depression (control practices) to control for any possible "attention" effect. In developing the educational intervention, the study team followed the five phases of the framework for the design and evaluation of complex health interventions proposed by the Medical Research Council and Campbell et al[34,35], and incorporated evidence from systematic reviews and guidelines on changing professional practice [36,37]. A brief 17-minute video depicting GP consultations with young people with FEP was shown to all members of the intervention practices, and the trial educators (first and second authors) then led a 15-minute question and answer session. The video addressed GP attitudes and negative stereotypes of people with FEP and also included elements of didactic factual teaching on, for example, links between drug use and psychosis, key warning symptoms of psychosis, including recognition of negative symptoms, and how to ask questions about sensitive issues such as hearing voices and suicidal ideas. A booklet summarising the content of the video and a two-sided laminated 'tip' sheet on FEP symptoms and useful questions to ask patients were also given to all intervention group GPs.

All intervention GPs viewed the video between November 2003 and January 2004. Twenty-one general practices (54%) viewed the video during 'protected learning' time and 18 general practices (46%) viewed the video at their premises during their own time. At the end of the education session, GPs were asked to evaluate three specific elements of the video on a five-point rating scale: key information on FEP, useful questions to ask during consultations, and personal confidence in detecting FEP. GPs were also asked what they found most and least useful about the video.

Refresher educational sessions for intervention practices were conducted in small groups, with training events spread over three days from 29 June 2004 to 1 July 2004. The refresher training consisted of personal testimonies from two service users, a service user personal testimony presented in a brief 10 minute video, and a presentation from an EIS representative on the EIS acceptance criteria and referral process. GPs were again asked to provide feedback on specific components of the training using a similar five-point rating scale.

### Outcomes

The primary outcome will be measured at practice level (unit of randomisation) by assessing the difference in the number of referrals of young people with FEP to secondary care services between study groups. Secondary outcomes are DUP, time to recovery, use of the Mental Health Act (at patient level), and GP consultation rate (at practice level). Instruments used in the evaluation are summarised in Table 2.

**Table 2 T2:** Summary of research assessments

Instrument	Baseline	Follow-up
SCAN [38]	x	
PANSS [41]	x	x
Insight Scale [39]	x	x
Early Signs Scale [40]	x	x
DUP [42]		x
PAS [44]		x
Encounter Form [45]		x

### Baseline assessments and follow-up

The two field researchers are approaching all new FEP referrals to the two EIS in inner-city Birmingham to seek informed consent and entry to the trial. Patients meeting eligibility criteria and providing written informed consent are interviewed by the research team at baseline and at a four-month follow-up interview. At baseline, data are collected on socio-demographic factors and psychosis symptoms during the past month using the Schedules for Clinical Assessment in Neuropsychiatry (SCAN) version 2.0 [38]. The SCAN is a set of instruments used to assess, measure, and classify psychopathology associated with adult major psychiatric disorders. Part two, which includes psychosis disorders, was felt most applicable for use in this study.

### Insight

Insight is measured at baseline and at four months using the Insight Scale [39], an eight-item self-report scale designed to be sensitive to changes in levels of insight. The scale captures each of three widely accepted dimensions of insight: awareness of illness, perceived need for treatment, and ability to re-label symptoms as pathological. Higher scores indicate greater levels of insight. The psychometric properties of the scale are excellent and it is a widely used scale in psychosis research.

### Early signs

The Early Signs Scale [40] is used at baseline and at four months to assess at risk mental states and provide a measure of clinical recovery, determined by ratings of <20 (including <10 on scales of incipient psychosis and disinhibition combined).

### Psychotic symptoms

Psychotic symptoms are measured at baseline and at four months with the Positive and Negative Syndrome Scale (PANSS; [41]). The PANSS is a 30-item semi-structured interview that consists of seven items assessing positive symptoms (e.g., hallucinations, delusions, conceptual disorganisation), seven items assessing negative symptoms (blunted affect, difficulty in abstract thinking) and 16 items assessing global psychopathology (e.g., depression, anxiety, disorientation). Items are scored between one (not present) and seven (severe). The PANSS is a widely used, valid and reliable measure of mental state.

### Duration of untreated psychosis (DUP)

At the four-month follow-up assessment, DUP is assessed with a semi-structured interview following the model of Beiser [42]. DUP is defined as the time interval between the onset of psychotic symptoms and the initiation of treatment, and calculated according to a stringent protocol adapted from criteria developed by Larsen [43].

### Premorbid functioning

Premorbid functioning is assessed at the four-month follow-up assessment with the Premorbid Adjustment Scale (PAS) [44]. The "premorbid" period is defined as the period that ends six months before there is any evidence of psychotic symptoms or first psychiatric hospital admission. The PAS measures four areas of development: (1) sociability-isolation, (2) peer relationships, (3) ability to function outside of the nuclear family, and (4) capacity to form intimate socio-sexual ties at each of four life stages: childhood (up to age 11), early adolescence (12–15 years), late adolescence (16–18 years), and adulthood (19 years and older). The PAS includes a 'general' scale that measures the highest level of functioning attained by the individual before becoming ill. For example, if an individual was aged 20 at the time of completion, but experienced psychotic symptoms at the age of 17, the adult scale would not be completed. Items are scored on a Likert-type scale of zero to six, with lower scores denoting healthier functioning and higher scores indicating greater dysfunctional adjustment.

### Pathways to care

Pathways to care is measured at four months follow-up with the Encounter form [45]. This instrument is also used to determine retrospective GP consultation and referral rates and use of the Mental Health Act from primary care records.

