### Sample size

The primary outcome of the study is the difference between the randomised groups on the number of young people with FEP referred to EIS during the study period, analysed on the basis of intention to treat. As the GPs, rather than their patients, are the subjects of the study, the statistical analysis and thus power calculation accounts for this.

Assuming the standard critical value for α (2 sided p = 0.05), and further that, on average, two referrals will be made in control practices in the study period, and that the variance for between practice variability is one, the study has 80% power (1-β) to detect a mean difference of 1.2 referrals between intervention and control practices, and 90% power (1-β) to detect a mean difference of 1.4 referrals.

As this study is the first randomised trial of an educational intervention in primary care which aims to influence detection and referral practice of GPs, we have no data upon which to base power calculations for the secondary outcome measures which may be considered exploratory (and which will provide relevant data for any future studies).

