### Blinding

The participants and field researchers assessing patient outcomes were blinded to the identity of practices that participated in the educational intervention. Statistical analysis follows a pre-specified analysis plan.

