## Discussion

The Redirect trial has been designed to evaluate the effectiveness of an educational intervention targeted at GPs on the detection of young people with FEP on referrals to EIS. The educational intervention was designed to be feasible to implement in a busy primary care setting and acceptable to GPs. Recruitment of practices into the trial itself was helped by ensuring that GP time and involvement in the study was kept to a minimum, in recognition of the workload pressures that many UK GPs currently face, particularly with the implementation of the new GMS GP contract [20]. All patients are therefore being recruited from the EIS.

The full support and co-operation of the PCTs, in particular the Heart of Birmingham PCT who enabled the study team to use the bi-monthly PCT protected learning time session to deliver the video based education, was also key to the success of implementing the intervention.

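### Use of the Mental Health Act is taken from the randomised practices' own records with no stated cross-check, so under-recording that differs by arm cannot be excluded

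*Protocol article*

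**What the plan says.** The Outcomes section lists the outcome and its level: "Secondary outcomes are DUP, time to recovery, use of the Mental Health Act (at patient level), and GP consultation rate (at practice level". The Sample size section gives the secondary outcomes their weight: "we have no data upon which to base power calculations for the secondary outcome measures which may be considered exploratory".

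The source is given under Pathways to care. The instrument and its timing come first, "Pathways to care is measured at four months follow-up with the Encounter form [45", and then the source: "This instrument is also used to determine retrospective GP consultation and referral rates and use of the Mental Health Act from primary care records".

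Three other places bear on it:

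- **Design and randomisation of general practices:** the practice is the randomised unit. "Practices were randomly allocated to either the intervention (39 practices) or control group (39 practices".
- **The educational intervention:** intervention GPs saw a video on first episode psychosis; control GPs had a session on cognitive behaviour therapy for depression.
- **Blinding:** "The participants and field researchers assessing patient outcomes were blinded to the identity of practices that participated in the educational intervention".

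The Strengths section describes patient outcomes differently, as resting on structured interviewing and what patients themselves report. The Discussion says of recruitment: "All patients are therefore being recruited from the EIS".

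**The concern.** The article names a source for this outcome, so this is a stated choice and not a detail left to a fuller document. The people who keep that source are the units that were randomised, and they know which topic they were taught. If the teaching changes how fully psychosis-related events are noted or filed, the completeness of the outcome data becomes a consequence of allocation. Masking whoever later reads the record cannot undo a difference that entered when the record was made.

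Two kinds of error are possible. If capture is incomplete but equal in the arms, an absolute difference shrinks. If capture differs by arm, a difference can appear where there is none, or a real one can be hidden. The Background section cites an association between GP involvement and less use of the Act, so readers will set this result against that claim. The Sample size section also expects the secondary outcomes to inform future studies, so a distorted estimate would carry forward.

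**Working it through.** **The plan's own figures.** The article gives no event rate, capture rate or power for use of the Mental Health Act. Its only power figures are for the primary outcome. With 39 practices per arm and variance per practice equal to the Poisson mean plus 1, power is Φ(d/√((v0+v1)/39) − 1.96). For d = 1.2, v0 = 3 and v1 = 4.2 give 79.8% (stated 80%). For d = 1.4, v1 = 4.4 gives 89.5% (stated 90%). Both reproduce and neither bears on this point.

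**The passages side by side.**

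| Question | Where | What it says |
|---|---|---|
| What is the source? | Pathways to care | Primary care records, retrospectively, on the Encounter form |
| What is the source? | Strengths | Structured interviewing and patients' own reports, for patient outcomes in general |
| Who keeps primary care records? | Design and randomisation | The practices, which are the randomised units |
| Do GPs know the topic they were taught? | The educational intervention | Psychosis in one arm, depression in the other; knowledge of the topic follows from having attended |
| Who is blinded? | Blinding | Participants and field researchers; GPs as record keepers are not mentioned |
| Is a mental health service record named? | Nowhere | No |

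**Illustration.** Every rate below is an assumption. Let p be true use and s the share of events that the record captures. The observed rate is p × s.

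*No true effect, capture 70% in control and 90% in intervention:*

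| True use, both arms | Control observed | Intervention observed | False difference | Odds ratio |
|---|---|---|---|---|
| 20% | 0.20 × 0.70 = 14% | 0.20 × 0.90 = 18% | +4 points | 1.35 |
| 40% | 0.40 × 0.70 = 28% | 0.40 × 0.90 = 36% | +8 points | 1.45 |
| 60% | 0.60 × 0.70 = 42% | 0.60 × 0.90 = 54% | +12 points | 1.62 |

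*Capture reversed (90% control, 70% intervention):* −4, −8 and −12 points, with odds ratios 0.74, 0.69 and 0.62.

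*A true effect, 40% control and 30% intervention (risk ratio 0.75):*

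- Equal capture of 80%: 32% and 24%, a difference of 8 points; ratio 24/32 = 0.75.
- Equal capture of 60%: 24% and 18%, a difference of 6 points; ratio 18/24 = 0.75.
- Capture 70% control, 90% intervention: 28% and 27%; ratio 27/28 = 0.96, so the effect almost disappears.
- Capture 90% control, 70% intervention: 36% and 21%; ratio 21/36 = 0.58, so the effect is exaggerated.

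**The case against.** The strongest reply is that no defect in the records has been shown.

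- **Completeness.** A reader might infer that detentions are in fact missed. The article says nothing about how complete these entries are, or about how news of a detention reaches a practice. This stands: the most that can be said is that events can be missed.
- **Direction.** A reader might infer that trained GPs record more, so that the intervention arm would look worse. The teaching as described covers symptoms, attitudes, consultation questions and the referral process, not record-keeping. This stands too: a difference by arm is possible, but its direction is unknown.
- **Safeguards.** Field researchers are blinded, and the control arm had its own session to balance attention. Both help. The first protects extraction, not the making of the record. The second balances contact, not the topic taught. That GPs know their topic is inferred from the design rather than stated, and the Blinding section does not say which participants it means.
- **Sole source.** The Encounter form is also the pathways-to-care instrument at four months, and Strengths speaks of interviews and self-report, so another source may exist. But the one sentence that assigns a source to this outcome names primary care records. The two sections therefore need reconciling, and the general remark does not settle the matter.
- **Simple under-recording leaves the risk ratio alone.** True, as the equal-capture lines show. The absolute difference still shrinks.
- **Reach.** Because the same sentence mentions referral rates, a reader might extend the point to the primary outcome. The article has the field researchers approach new referrals at the two EIS and recruits all patients there, so it does not support that extension.

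**Conclusion.** The point holds in a limited form. The article fixes the records of the randomised practices as the source for use of the Mental Health Act, names no independent check, and describes the source of patient outcomes differently elsewhere. Under-recording, possibly differing by arm, cannot be excluded. Whether it occurs, how large it is and which way it runs cannot be learned from the document.

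The illustrative errors, 4 to 12 points in either direction under no true effect and a loss of 2 to 4 points from a true 10-point difference, rest wholly on the assumed rates. They show scale and are not estimates. The outcome is secondary, unpowered and described as exploratory, and the primary outcome and its power calculation are untouched. This is a cheap improvement, not a flaw that threatens the trial.

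**What to change.** In Pathways to care:

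1. Make the EIS or mental health service record the main source for use of the Mental Health Act, recorded as yes/no with the date.
2. Have it extracted by the field researchers who are already blinded to which practices had the intervention.
3. Use a window of the same length for every patient, for example a set number of months ending at the four-month follow-up. It should not start at symptom onset: its length would then vary with the delay that earlier referral is meant to shorten, and exposure time could differ by arm.
4. Keep primary care records as a cross-check, and report agreement between the two sources by arm.
5. Reword Pathways to care and Strengths so that they give the same source for this outcome.

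The cost is a short record look-up for each consented patient. If the window reaches back before EIS referral, the look-up must cover the wider mental health service record and not the EIS notes alone. Sample size, randomisation and the primary analysis do not change.
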